## Abstract

**Background:**

Treatment with Androgen Deprivation Therapy (ADT) for prostate cancer is associated with changes in body composition including increased fat and decreased lean mass; increased fatigue, and a reduction in quality of life. No study to date has evaluated the effect of dietary and physical activity modification on the side-effects related to ADT. The aim of this study is to evaluate the efficacy of a 6-month dietary and physical activity intervention for prostate cancer survivors receiving ADT to minimise the changes in body composition, fatigue and quality of life, typically associated with ADT.

**Methods:**

Men are recruited to this study if their treatment plan is to receive ADT for at least 6 months. Men who are randomised to the intervention arm receive a home-based tailored intervention to meet the following guidelines a) ≥ 5 servings vegetables and fruits/day; b) 30%-35% of total energy from fat, and < 10% energy from saturated fat/day; c) 10% of energy from polyunsaturated fat/day; d) limited consumption of processed meats; e) 25-35 gm of fibre/day; f) alcoholic drinks ≤ 28 units/week; g) limited intake of foods high in salt and/or sugar. They are also encouraged to include at least 30 minutes of brisk walking, 5 or more days per week. The primary outcomes are change in body composition, fatigue and quality of life scores. Secondary outcomes include dietary intake, physical activity and perceived stress. Baseline information collected includes: socio-economic status, treatment duration, perceived social support and health status, family history of cancer, co-morbidities, medication and supplement use, barriers to change, and readiness to change their health behaviour. Data for the primary and secondary outcomes will be collected at baseline, 3 and 6 months from 47 intervention and 47 control patients.

**Discussion:**

The results of this study will provide detailed information on diet and physical activity levels in prostate cancer patients treated with ADT and will test the feasibility and efficacy of a diet and physical activity intervention which could provide essential information to develop guidelines for prostate cancer patients to minimise the side effects related to ADT.

**Trial registration:**

ISRCTN trial number ISCRTN75282423

## Background

Prostate cancer is the most common cancer in men in the United Kingdom, with more than 35,000 new cases diagnosed each year [1]. The number of prostate cancer survivors is increasing each year due to advances in cancer detection, treatment and care. Recent statistics (2001-2006) have shown that, in the absence of other competing causes of death, an estimated 77% of those diagnosed with prostate cancer can expect to be alive in 5 years, whereas in 1991-1995 the five-year survival rate was estimated at < 54% [1]. Therefore, as the number of prostate cancer survivors and their length of survival increases, health issues specific to prostate cancer survival are fast emerging as a public health concern.

Treatment of prostate cancer is based on a patient's age, co-morbidity, stage and grade of the prostate tumour and local availability of treatment [2]. Standard therapies for localised prostate cancer include radical prostatectomy, external beam radiotherapy, brachytherapy, often combined with androgen deprivation therapy (ADT). For more advanced prostate cancer ADT is a standard part of the management for the majority of patients and has been conclusively shown to improve survival [3]. Because of increasing evidence of the benefit of ADT in prostate cancer, the number of prescriptions of ADT for treating prostate cancer in the UK increased from 33,000 in 1987 to 470,000 in 2004 [4]. However, treatment with ADT is associated with significant adverse physiological and psychological effects. For example, the reduction in testosterone levels by ADT causes a decrease in lean body mass and muscle strength, a reduction in bone mass and bone mineral density, an increase in fat mass, total body weight and cholesterol levels; a reduction in haemoglobin levels and as a result increased lethargy, which can affect both physical and physiological function [5-7].

A diet and physical activity intervention that could address some of these side effects could be beneficial to prostate cancer patients treated with ADT. Experimental studies examining the role of exercise during ADT treatment for prostate cancer have shown that 10-20 weeks of exercise is an effective way to reduce fatigue and depression, improve quality of life, increase muscular fitness and strength [8-11], and improve physical functional capacity preventing adverse effects on body composition [9]. Indeed 20 weeks of exercise has been shown to preserve lean body mass and prevent an increase in fat mass [11]. Changes in dietary intake at the time of treatment may also help to counteract the changes in body composition associated with ADT. Several randomised controlled trials (RCTs) of diet and physical activity interventions in prostate cancer patients have begun in recent years and include the FRESH START trial, Project LEAD, and RENEW. However the men recruited within these studies have received all types of treatment modalities [12-14]. Therefore, the impact of a diet and physical activity intervention on the side-effects related to ADT, a group that experiences major changes in body composition, has not yet been discussed in any of these studies.

To date very little information is known about dietary intake and physical activity levels of prostate cancer patients in the UK. In general however, cancer patients are highly motivated to seek information about food choices, physical activity, dietary supplement use, and complementary nutritional therapies in an attempt to improve their response to treatment, speed-up recovery rates, reduce the risk of cancer recurrence, and/or to improve their quality of life [15]. The American Cancer Society has recently published nutrition and lifestyle guidelines for cancer survivors [16] although the impact of these guidelines on outcomes relevant to prostate cancer patients treated with ADT are unknown. In addition, for long-term prostate cancer survivors, an appropriate weight, a healthy diet, and a physically active lifestyle aimed at preventing recurrence, second primary cancers, and other chronic diseases should be a priority. Therefore, we have developed an intervention aimed at encouraging patients treated with ADT to meet healthy eating guidelines and achieve at least 30 minutes of brisk walking at least 5 days per week to reduce treatment related side-effects and improve overall quality of life.

### Objectives

#### Primary objective

The study is intended to evaluate the efficacy of a 6 month dietary and physical activity intervention for prostate cancer survivors receiving ADT. The outcomes of interest are body composition, fatigue and quality of life.

#### Specific objectives

We will also describe the nutritional status, dietary intake and physical activity level among prostate cancer survivors in Northern Ireland. The effect of the intervention on dietary intake, level of physical activity, quality of life, fatigue, and psychological stress will be assessed by comparing the intervention group with the controls. Moreover the stages of readiness to change lifestyle behaviours in prostate cancer survivors after diagnosis and during ADT will be measured using the transtheoretical model.

#### Hypothesis

We hypothesize that a diet and physical activity intervention will prevent or reduce weight gain, and minimize the increase in body fat mass typically found in patients treated with ADT in the intervention group compared with the controls. We also hypothesize that the intervention patients will experience less fatigue and will have a better quality of life score compared with the controls.

## Method

### Design

Patients are randomised either to receive the dietary modification and physical activity intervention or standard care (control group) with a 1:1 allocation ratio (Figure 1).

**Figure 1 F1:**
[figure not shown]
**Study Design in flow diagram**. Recruitment, randomisation, follow-up and outcomes assessment.

### Setting and participants

Prostate cancer patients are recruited from the Cancer Centre at Belfast City Hospital, Belfast, Northern Ireland, United Kingdom. Our inclusion and exclusion criteria are as follows.

### Inclusion criteria

1) histologically proven adenocarcinoma of prostate; and 2) commencing Lutenising Hormone Releasing Hormone Agonist (LHRHa) therapy for at least 6 months or already being treated with LHRHa and planned to continue for at least a further 6 months

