### Sample size

This study is an exploratory one and so formal power calculations are difficult. The primary endpoint used to calculate sample size was body composition. Smith *et al *[17] presented data from a study of prostate cancer patients treated with hormone therapy and the mean percentage change in fat mass following ADT treatment was 9.4% (SD = 9.6%). If it is assumed that the controls in the planned study will have a similar percentage of fat mass, then with 36 patients in the intervention group and 36 patients in the control group the study will have 90% power at 5% significance to detect a mean percentage change in fat mass of 7.4% between the control and intervention group. An additional 30% was added to the sample size calculation to account for non-compliance and potential drop-out or discontinuation. Therefore 47 patients will be randomised to the intervention and 47 randomised to the control group. This sample size will also allow us to detect a 3.4 point (SD = 5.0 points) difference in Fatigue Severity Score [8] (a 3 point difference on the fatigue scale is considered to be the minimal clinically important difference) [18]; and a 6.0 point (SD = 9.0 points) difference on the Functional Assessment of Cancer Therapy-General (FACT-G) score [8].

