### Statistics

The data collected in the trial will be analysed based on intention to treat and lost to follow-up cases will be considered as missing observations [38]. Change over the treatment period will be calculated by subtracting the baseline value from the value at month 3 and month 6. Primary and secondary endpoints between those assigned to the intervention and control group will be compared using analysis of covariance (ANCOVA) with baseline scores included in the models as covariates. Skewed data will be log transformed prior to inclusion in the ANCOVA models. The trial outline conforms to the Consort statement guidelines.

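### Men starting LHRHa and men already on it are analysed together without ADT status at entry as a covariate, and the planning assumption is worded for the wrong quantity

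*Protocol article*

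**What the plan says.** **Population.** The Inclusion criteria accept men commencing LHRHa for at least 6 months, "or already being treated with LHRHa and planned to continue for at least a further 6 months". The article sets no upper limit on earlier treatment and gives no expected share of each group.

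**Planning.** The Sample size section cites a 9.4% mean change in fat mass following ADT (SD 9.6%) from an earlier study of men on hormone therapy. It links that study to this trial with the words "If it is assumed that the controls in the planned study will have a similar percentage of fat mass", and then claims "90% power at 5% significance to detect a mean percentage change in fat mass of 7.4% between the control and intervention group" with 36 men per arm. It calls the study exploratory and says that formal power calculations are difficult.

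**Allocation.** The Randomisation section describes one computer-generated sequence in permuted blocks of four. It names no strata.

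**Analysis.** The Statistics section compares the arms by ANCOVA, "with baseline scores included in the models as covariates". It names no other covariate.

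**Data.** The abstract states: "Baseline information collected includes: socio-economic status, treatment duration". The Other assessments section adds that treatment details are taken from the medical notes. Neither is given a role in allocation or in the stated model. Only readiness to change is said to be taken into consideration in the analysis.

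**The concern.** Under the Hypothesis section, the intervention should limit the fat gain typical of ADT. A man who has been on LHRHa for some time may have had part of that gain before his baseline visit, so his further 6-month change may differ from that of a man just starting. His baseline fat score does not show this: two men with the same score can be at different points of treatment. If status at entry does predict further gain, leaving it out puts explainable variation into the residual and leaves any chance difference in mix between the arms unadjusted.

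The planning assumption has a related fault. A similar percentage of fat mass is a level, whereas the calculation is about percentage change. As worded, the assumption does not carry the planning change over to this trial, and it does not raise the question of whether that change fits men already treated.

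**Working it through.** **1. The plan's own figure.** Inputs from the Sample size section: difference 7.4, SD 9.6, 5% significance (two-sided taken, since it reproduces the figure), 90% power.

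n per arm = 2 × (1.960 + 1.282)² × 9.6² / 7.4² = 35.4, so 36. Power at 36 per arm is 90.5% by the normal formula and 89.7% by noncentral t. Adding 30% gives 36 × 1.3 = 46.8, so 47. The stated figures reproduce. The 9.4% does not enter this formula.

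**2. Power in a mixed population (assumed ranges).** The documents give neither the share already treated (p) nor those men's further 6-month control gain (g). I assume:
- p = 25% or 50%, and g from 0 to 9.4%;
- starters in the control arm gain 9.4%;
- the intervention removes 7.4/9.4 = 0.787 of any gain;
- the SD within each status group is 9.6.

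Formulas:
- Difference = 0.787 × [9.4(1 − p) + g·p].
- Gap between starters and men already treated: 9.4 − g in controls, and 0.213 × (9.4 − g) in the intervention arm.
- Unadjusted variance in each arm = 9.6² + p(1 − p) × gap². The two arms' variances are then averaged.
- Adjusted SD = 9.6.

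Example, p = 50%, g = 0: difference 3.70; gaps 9.4 and 2.0; average variance 92.16 + 0.25 × (88.36 + 4.00)/2 = 103.7; SD 10.18.

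Power by noncentral t, 36 per arm:

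| p | g | Difference | Unadjusted | With ADT status |
|---|---|---|---|---|
| 25% | 0 | 5.55 | 64% | 68% |
| 25% | 3 | 6.14 | 75% | 76% |
| 25% | 4.7 | 6.48 | 80% | 81% |
| 25% | 9.4 | 7.40 | 90% | 90% |
| 50% | 0 | 3.70 | 33% | 36% |
| 50% | 3 | 4.88 | 54% | 57% |
| 50% | 4.7 | 5.55 | 66% | 68% |
| 50% | 9.4 | 7.40 | 90% | 90% |

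The covariate recovers 0 to 4 points (at most 67.7% − 63.8% = 3.9). The rest of any loss comes from the smaller assumed difference, which adjustment cannot restore. Like the plan's own calculation, the table ignores the gain from adjusting for the baseline score.

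**3. Chance imbalance.** With half the men already treated and 47 per arm, the SD of the between-arm difference in share is √(2 × 0.25/47) = 0.103, about 10 percentage points.
- Intervention without effect and g = 0: one SD shifts the difference by 0.103 × 9.4 = 0.97 points, or 13% of 7.4. This is the extreme case.
- Planned effect, g = 0: √(0.25/47) × √(9.4² + 2.0²) = 0.0729 × 9.61 = 0.70 points.
- Planned effect, g = 3: 0.0729 × √(6.4² + 1.36²) = 0.48 points.
- g = 9.4: no shift.

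For comparison, the standard error of the difference with SD 9.6 is 9.6 × √(2/47) = 1.98 at 47 per arm and 9.6 × √(2/36) = 2.26 at 36.

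**The case against.** The strongest case on the other side has five parts.

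- **Dilution is not documented.** A reader might infer that the planned effect is diluted and the trial underpowered. That needs a source cohort of new starters, fat gain that slows with time on ADT, and a material share of men already treated. The article states none of these. If men already treated gain as fast as starters, power stays at 90%. This objection stands.
- **The sample size does not rest on 9.4.** It follows from 7.4 and 9.6 alone, and the article never defines 7.4 as a fraction of 9.4. The proportional model above is this review's assumption. This also stands. The condition remains that 7.4 must apply to the men actually enrolled.
- **Randomisation protects the comparison.** A reader might infer that chance imbalance could pass as a treatment effect. The documents do not support that as a claim of bias: allocation is random, the estimate is unbiased in expectation, and the test's error rate already allows for such imbalance. Baseline fat, which is adjusted for, may also carry part of any earlier gain. What remains is a modest question of precision and interpretation.
- **A SAP may add covariates.** It may, and an article condenses. But the Statistics section states a model, and the proposal improves that model.
- **Stratification and an interaction test are matters of preference.** Unstratified blocks are valid, the envelopes are already made up, and an interaction at about 36 per arm would be very imprecise. This stands. Nor do the documents support inferring that the effect exists only in starters.

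**Conclusion.** The point holds in a limited form. The article mixes two groups that may differ in the fat gain still to come, records what separates them, and leaves it out of both allocation and the stated model. The cost in precision is small: about 0 to 4 power points under the assumed mixes, with an imbalance shift of about 0.5-0.7 points per SD under the planned effect (half already treated, further gain 0-3%) and about 1.0 only in the extreme no-effect case. The planning sentence names a level where it needs a change.

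The 90% power depends on a 7.4-point difference in the mixed population. Without adjustment it could lie anywhere from 64% to 90% (a quarter already treated) or from 33% to 90% (half already treated). These ranges rest on the proportional-effect assumption and on shares and gains that the documents do not give. They show sensitivity and do not establish a shortfall. That ADT status predicts further gain is plausible, but the article does not show it.

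**What to change.** 1. In the Statistics section, add ADT status at entry (commencing versus already treated) as a prespecified covariate beside the baseline score in the primary ANCOVA models, with months on LHRHa as a sensitivity version. The data are already collected, so the cost is one sentence and one model term.
2. In the Sample size section, change the assumption so that controls are taken to have a similar percentage change in fat mass, and state that the 90% power holds only if a 7.4-point difference also applies in a population mixing starters and men already treated. This is a wording change. A short sensitivity table like the one above would be useful.
3. If effects by ADT status are reported, present them as descriptive estimates with confidence intervals only.
4. Optional: stratify any remaining envelopes by ADT status. This needs a second envelope series from the independent researcher and is worth doing only if enough recruitment remains.

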### Exclusion criteria

1) co-morbid conditions that limit physical activity such as severe cardiac disease, recent myocardial infarction, severe asthma or breathlessness, uncontrolled hypertension (blood pressure > 160/95 mm/Hg), or severe pain; 2) medical conditions that require a reduced fruit and vegetable diet (e.g. kidney failure); 3) history of insulin dependent diabetes; 4) treated with any type of steroid hormone; 5) treated for any other cancer; and 6) life expectancy of less than 2 years.

### Sample size

This study is an exploratory one and so formal power calculations are difficult. The primary endpoint used to calculate sample size was body composition. Smith *et al *[17] presented data from a study of prostate cancer patients treated with hormone therapy and the mean percentage change in fat mass following ADT treatment was 9.4% (SD = 9.6%). If it is assumed that the controls in the planned study will have a similar percentage of fat mass, then with 36 patients in the intervention group and 36 patients in the control group the study will have 90% power at 5% significance to detect a mean percentage change in fat mass of 7.4% between the control and intervention group. An additional 30% was added to the sample size calculation to account for non-compliance and potential drop-out or discontinuation. Therefore 47 patients will be randomised to the intervention and 47 randomised to the control group. This sample size will also allow us to detect a 3.4 point (SD = 5.0 points) difference in Fatigue Severity Score [8] (a 3 point difference on the fatigue scale is considered to be the minimal clinically important difference) [18]; and a 6.0 point (SD = 9.0 points) difference on the Functional Assessment of Cancer Therapy-General (FACT-G) score [8].

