## Discussion

As far as we are aware, this is the first RCT to assess whether a combined diet and physical activity intervention can attenuate the negative changes in body composition associated with use of ADT in prostate cancer patients and also to assess its impact on fatigue and quality of life. The intervention period in the present study is longer than previous studies (12-20 weeks of physical activity interventions [8-11]) and, in keeping with current views that initiation and maintenance of a diet and physical activity modification for cancer survivors should be tailored to the survivor's condition and personal preferences [16], it is individually tailored to the patient. Moreover, patients' readiness to change lifestyle behaviours using the transtheoretical model is considered during the delivery of the intervention. This model has been used successfully in previous diet and exercise intervention studies [12,13,39]. We expect that by using these approaches we will increase compliance and achieve the greatest possible change in behaviour and in the outcomes of interest. The intervention is also home rather than hospital based and is therefore more likely to be sustained in this older population group [13,14,40,41]. Moreover, the study sample size is sufficient to detect a clinically relevant change in body composition and the study includes a range of validated physiological and psychological assessments, which will maximise the internal validity of the study.

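### Multiplying 36 by 1.3 keeps 36 analysable men per arm only up to about 23% loss, and a head-count top-up does not correct for non-compliance under intention to treat

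*Protocol article*

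**What the plan says.** The Sample size section takes from a cited study a mean fat-mass change of 9.4% with SD 9.6%. For 36 men per arm it states that "the study will have 90% power at 5% significance"; the target is a 7.4% difference between the arms in fat-mass change. On the allowance it says: "An additional 30% was added to the sample size calculation to account for non-compliance and potential drop-out or discontinuation". This brings each arm to 47 randomised men.

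The section calls the study exploratory. It does not say what loss is expected or how the 30% divides between non-compliance and drop-out.

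On the analysis, the Statistics section says: "The data collected in the trial will be analysed based on intention to treat". Men lost to follow-up are treated as missing, and the arms are compared by ANCOVA with the baseline value as covariate. The Compliance and drop-outs section keeps men who leave in the analysis until they leave. The Discussion states that "the study sample size is sufficient to detect a clinically relevant change in body composition".

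**The concern.** Two different problems are handled with one multiplier, and it fits neither well.

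- **Loss of data.** An allowance for loss should leave the required number after the loss has occurred, so the required number is divided by the retained fraction. Multiplying by 1.3 protects against a smaller loss than 30%.
- **Non-compliance.** A man who does not follow the advice but attends at 6 months costs no sample size under intention to treat. If he gains less, he reduces the mean difference between the arms. With a non-compliant fraction c that gains nothing, the difference falls by the factor (1 - c) and the required number rises by 1/(1 - c)^2. Adding men one for one does not achieve this.

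At stake is how the 90% figure and the Discussion's sufficiency statement are read. In a home-based lifestyle trial partial adherence is a realistic possibility, and the authors themselves allow for it. A reader of a null result should know under what loss and adherence the stated power applies.

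**Working it through.** **Inputs from the Sample size section:** difference 7.4, SD 9.6, significance level 5%, power 90%, 36 per arm before and 47 per arm after the allowance, allowance 30%. Sidedness is not stated. Two-sided is assumed because it gives 36 per arm, whereas one-sided gives 29.

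**1. The plan's own figures.** n per arm = 2(1.96 + 1.2816)^2 x 9.6^2 / 7.4^2 = 35.4, so 36. Power with 36 per arm is 90.5% by normal approximation and 89.7% by noncentral t. The base figure reproduces. 36 x 1.3 = 46.8, so 47 also reproduces.

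**2. What 47 per arm protects.**
- Tolerated loss: (47 - 36)/47 = 11/47 = 23.4%.
- Number needed to keep 36 after 30% loss: 36/0.7 = 51.4, so 52 per arm (104 in total against 94).
- Left after 30% loss from 47: 47 x 0.7 = 32.9, about 33 per arm.

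| Analysed per arm | Power for 7.4 (t) | Power for 7.4 (normal) | Difference detectable with 90% power (t) |
|---|---|---|---|
| 47 (no loss) | 95.9% | 96.2% | – |
| 36 (23.4% loss) | 89.7% | 90.5% | 7.44 |
| 33 (30% loss) | 86.9% | 87.9% | 7.78 |

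On the normal approximation the detectable difference with 33 per arm is 7.66.

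**3. Possible gain from ANCOVA (assumption; no correlation is given).** With 33 per arm and correlation r between baseline and change, the residual SD is 9.6 x sqrt(1 - r^2). For r = 0.2, 0.3 and 0.4, power by noncentral t is about 88%, 90% and 92%.

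**4. Dilution under intention to treat (assumptions: 7.4 is the difference under full compliance, non-compliers in the intervention arm gain nothing, unadjusted t-test).** With 47 per arm and no loss the difference is 7.4 x (1 - c):
- c = 10%: 7.4 x 0.90 = 6.66, power 91%.
- c = 12%: 7.4 x 0.88 = 6.51, power 90%.
- c = 15%: 7.4 x 0.85 = 6.29, power 88%.
- c = 30%: 7.4 x 0.70 = 5.18, power about 74% (73.5% t, 74.4% normal). For 90% power about 73 to 74 per arm would be needed, compared with 36/0.7^2 = 73.5.

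With 15% loss and 15% non-compliance, 47 x 0.85 = 39.95, about 40 per arm are analysed:
- If the 15% is of retained men, the difference is 7.4 x 0.85 = 6.29 and power is 82%.
- If the 15% is of randomised men, the share among those retained is 0.15/0.85 = 17.6%, the difference is 6.09 and power is 80% (81% normal).

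**The case against.** A reader might infer that the stated 90% power is not delivered. The article does not support that. It attaches 90% to 36 against 36, which is correct. It says that 30% was added, and 36 plus 30% is 47, so the sentence agrees with its own arithmetic. Nowhere does it say that 30% of men are expected to be lost. If 7.4% is the intention-to-treat difference, 90% power holds for any loss up to about 23%.

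Further points on the other side also stand:
- Multiplying instead of dividing costs only 2 to 3 points even if the whole 30% is lost, and a baseline correlation of about 0.3 would recover this.
- The low figures for dilution need a split of the 30% that is not given, 7.4% to be a full-compliance difference, and non-compliers to gain nothing. If 7.4% already reflects imperfect compliance, applying dilution counts it twice.
- The Discussion sentence names neither 90% nor 7.4%, so 87% power does not contradict it.

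What the objection does not remove is the mismatch between an allowance for non-compliance and the stated intention-to-treat analysis. The section fixes 7.4% first and then adds men for non-compliance. If 7.4% already included non-compliance, that addition has no purpose; if it did not, the addition is of the wrong kind. The sentence needs correcting on either reading.

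**Conclusion.** The point holds as a fault in the sample-size rationale, not as proof that the trial is underpowered.

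- **Loss.** 47 per arm protects 36 analysable men up to about 23% loss. At 30% loss about 33 remain, with about 87% power for 7.4% and a detectable difference of 7.8% against 7.4% with 36 (two-sided 5%, SD 9.6%, unadjusted t-test). ANCOVA may offset this shortfall.
- **Non-compliance.** It belongs in the assumed difference, not in the head count. Its cost in power cannot be fixed from the article. Under the assumptions labelled in the working, the cases shown run from about 91% (10% non-compliance, no loss) to about 74% (30% non-compliance, no loss). The 74% case puts the entire allowance on non-compliance and is an extreme, not an expectation.

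**What to change.** Keep 47 per arm and reword.

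1. In Sample size, replace the inflation sentence with, for example:

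> With 47 men randomised per arm, 36 remain for analysis if at most about 23% are lost, which keeps about 90% power for an intention-to-treat difference of 7.4%. At 30% loss about 33 per arm remain, with about 87% power (two-sided 5% t-test, SD 9.6%, no baseline adjustment).

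2. Delete non-compliance from the inflation, and state whether 7.4% is the difference under full compliance or the intention-to-treat difference.
3. If it is the full-compliance difference, add the power for a diluted difference and label the assumptions (non-compliers gain nothing, unadjusted t-test): about 91% at 10% and 74% at 30% non-compliance with no loss; about 80 to 82% with 15% loss and 15% non-compliance, saying whether the latter 15% is of randomised or retained men.
4. In the Discussion, make the sufficiency statement conditional on these figures.

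The cost is wording only. No extra men are needed and the design does not change; the stated power becomes conditional and, in some scenarios, less favourable.
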